#### Descriptions of costing procedure

Costs will be estimated from the healthcare and societal perspective during the one year of follow-up. *Direct health care costs* will be calculated by adding the costs derived from medication consumption (antidepressants and anxyolitics), medical tests, use of health-related services, and cost of staff to run the intervention. The cost of medication will be calculated by determining the price per milligram during the study, according to the Vademecum International (Red Book; edition 2013), including value-added tax. Total costs of medications will be calculated by multiplying the price per milligram by the daily dose in milligrams and the number of days receiving such treatment. The main source of unit cost data related to public medical tests and use of health services will be provided by the tariffs published in the Official Government Board of each Autonomous Community participating in the study. Tariffs for private sector will be obtained in each region consulting the last published tariff and inflated to 2013 using national Consumer Price Index. *Indirect costs* will be calculated considering the days on sick leave and multiplying them by the minimum daily wage in Spain for 2013. Finally, total costs will be calculated by adding direct and indirect costs. The unit costs will be expressed in Euros (€) based on prices in 2013.

#### Utilities

These represent the rating of the patients’ quality of life on a scale from 0 (as bad as death) to 1 (perfect health). Negative values are possible indicating a health state that is “worse than death”. Patients describe their quality of life using the EQ-5D, which is preferred for economic evaluations from a societal perspective. Quality Adjusted Life Years (QALYs) are calculated using Spanish tariffs of EQ-5D.

#### Cost-utility analysis

Cost-utility is explored through the calculation of incremental cost-utility ratios (ICUR), defined as the difference in mean costs divided by difference in mean QALYs [55]. As the duration of the study is 12 months, neither costs nor outcomes are subject to discounting. QALYs gained in each evaluation are approximated by using the area under-the-curve technique. To gain insight into the uncertainty around the pooled mean ICUR, we will plot the pooled bootstrapped cost-effect pairs on cost-utility planes. Bootstrapping involves resampling with replacement from the original sample a sufficiently large number of times in order to approximate the distribution of the population from which the original data are drawn [56]. In our analyses, 1,000 samples will be generated. This distribution is used to calculate the probability that each of the treatments is the optimal choice, subject to a range of possible maximum values (ceiling ratio) that a decision-maker might be willing to pay for a unit improvement in outcome. Cost-utility acceptability curves are presented by plotting these probabilities for a range of possible values of the ceiling ratio [57]. The acceptability curve represents the probability that the intervention is cost-effective, given a varying threshold for the willingness to pay for each QALY gained. The curves obtained incorporate the uncertainty that exists around the estimates of expected costs and expected effects associated with the intervention [58].

We assume that data will be missing completely at random. Only patients with both cost and relevant outcome data at 12-month follow-up will be included in the cost-utility analyses. Notwithstanding, the robustness of the cost-utility results will be tested by also imputing missing 12-month data (sensitivity analysis). The imputations will be performed using the multiple imputation procedure in STATA 11.0.

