**Methods:**

The study is made up of 3 phases: 1.- Development of a computerized cognitive-behaviour therapy for depression tailored to Spanish health system. 2.- Multicenter controlled, randomized study: A sample (N=450 patients) with mild/moderate depression recruited in primary care. They should have internet availability at home, not receive any previous psychological treatment, and not suffer from any other severe somatic or psychological disorder. They will be allocated to one of 3 treatments: a) Low intensity Internet-delivered psychotherapy + improved treatment as usual (ITAU) by GP, b) Self-guided Internet-delivered psychotherapy + ITAU or c) ITAU. Patients will be diagnosed with MINI psychiatric interview. Main outcome variable will be Beck Depression Inventory. It will be also administered EuroQol 5D (quality of life) and Client Service Receipt Inventory (consume of health and social services). Patients will be assessed at baseline, 3 and 12 months. An intention to treat and a per protocol analysis will be performed.

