#### Secondary outcomes

Socio-demographic variables. The following socio-demographic data will be collected: gender, age, marital status (single, married/relationship, separated/divorced, and widowed), education (years of education), occupation, economical level (in relation with Spanish minimum monthly salary that at the moment of the study was 640€).

Mini-International Neuropsychiatric Interview (MINI). This is a short structured diagnostic psychiatric interview that yields key DSM-IV and ICD-10 diagnoses [42]. MINI can be administered in a short period of time and clinical interviewers need only a brief training. The MINI has been translated and validated in Spanish [43].

EuroQoL-5D questionnaire (EQ-5D – Spanish version) [44]. Generic instrument of health-related quality of life. It has two parts: Part 1 records self-reported problems in each of five domains: mobility, self-care, usual activities, pain/discomfort and anxiety/depression. Each domain is divided into three levels of severity corresponding to no problems, some problems, and extreme problems, which allows obtaining a population-based preference score or societal index (SI). A total of 243 theoretically possible health states can be obtained and the SI is calculated on the basis of these health states. Values range from 1 (best health state) to 0 (death). However, this index may also provide negative values that correspond to health states perceived as worse than death. Utility scores for these health states were assigned using the readily available Spanish population tariffs [45]. Part 2 records the subject's self-assessed health on a VAS, a 10 cm vertical line on which the best and worst imaginable health states score 100 and 0, respectively.

Client Service Receipt Inventory – adapted (CSRI – Spanish version) [41,46]. Questionnaire for collecting information about use of healthcare and social care services and other economic impacts (such as time off work due to illness). The variant used in this study was designed to collect retrospective data on service utilization during the previous months after the last assessment. Data on baseline assess the previous three months before inclusion.

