### Analysis strategy

#### Analysis of clinical efficacy

The analysis will be per intent to treat and will follow CONSORT recommendations [54]. First, the three groups will be compared in order to verify that there are no significant differences among them at baseline to confirm they are comparable after randomization.

For comparisons, the ANOVA for continuous variables and the Chi-squared test for categorical variables will be used. Non-parametric tests may also be used. To confirm main hypothesis, an analysis of variance (ANOVA) of repeated measures, including all the assessments over the time, will be carried. The main outcome, scoring of BDI-II, will be used as continuous variable. Models will include adjustment by baseline value of BDI-II and any other variable that show differences among groups at baseline. Possible interactions Group × Time will be assessed using Mixed Factorial Anova (3 × 4: 3 groups by 4 temporal moments). Other linear regression models will be used to compare differences in BDI-II scoring among groups for each assessment over the time compared to baseline. Similar analysis will be carried out for secondary outcomes. For missing values a sensitivity analysis will be used to estimate the effect of missing values. Those valued will be replaced using different systems such as last registered values and imputations.

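### The cost-utility analysis names no adjustment for baseline EQ-5D utility, so a chance baseline difference passes partly into the QALY difference and precision is lost

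*Protocol article*

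**What the plan says.** The *Cost-utility analysis* section of the protocol article builds QALYs from repeated EQ-5D measurements: "QALYs gained in each evaluation are approximated by using the area under-the-curve technique". The incremental cost-utility ratio (ICUR) is "defined as the difference in mean costs divided by difference in mean QALYs". For uncertainty, "we will plot the pooled bootstrapped cost-effect pairs on cost-utility planes", using 1,000 samples. The *Utilities* section adds that "Quality Adjusted Life Years (QALYs) are calculated using Spanish tariffs of EQ-5D". Neither section mentions a regression model or a covariate. The economic analysis set is patients with cost and outcome data at 12 months, on the assumption that data are missing completely at random. Imputation is a sensitivity analysis.

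The *Analysis of clinical efficacy* section does adjust: "Models will include adjustment by baseline value of BDI-II and any other variable that show differences among groups at baseline". It then states: "Similar analysis will be carried out for secondary outcomes". Nothing there refers to QALYs, costs or the ICUR.

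The baseline data exist. Table 1 lists EQ-5D at baseline, and the CSRI entry under *Secondary outcomes* says: "Data on baseline assess the previous three months before inclusion".

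**The concern.** The area under the utility curve starts at the baseline value, so a difference between arms that existed before treatment is counted in the QALY difference. It also enters indirectly, because patients with better utility at baseline tend to have better utility later. If the section is followed as it stands, the QALY denominator of the ICUR, the cost-utility plane and the acceptability curves all depend on how baseline utility happened to fall across the arms.

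Two things are at stake. The first is precision: baseline utility predicts the QALY, and an analysis that ignores it has a larger standard error than the data allow. The second is credibility. If a visible imbalance appears, choosing between an unadjusted and an adjusted ratio after seeing the data is open to challenge.

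**Working it through.** The protocol article gives no QALY difference, utility SD, correlation or ICUR, so there is no stated figure to reproduce. The check concerns the mechanism and its likely size.

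**Inputs from the protocol article**
- Visits: the abstract says "Patients will be assessed at baseline, 3 and 12 months".
- Patients: 150 per arm and 30% expected withdrawal (*Sample size*), so 150 × 0.70 = 105 per arm at 12 months.

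**Assumed inputs**
- Utility SD 0.25 (range 0.15 to 0.30).
- Correlation ρ between baseline and each follow-up utility of 0.5 (range 0.3 to 0.7).

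**Step 1: weights.** Each visit's trapezoid weight is half the sum of its adjacent intervals, in years.
- Baseline: 0.25/2 = 0.125.
- Month 3: (0.25 + 0.75)/2 = 0.50.
- Month 12: 0.75/2 = 0.375.

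**Step 2: pass-through.** With equal SDs, a baseline difference D adds on average (0.125 + 0.875ρ) × D to the QALY difference.

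| ρ | Share of D passed on | Shift if D = 0.05 |
|---|---|---|
| 0 (direct only) | 0.125 | 0.006 |
| 0.3 | 0.3875 | 0.019 |
| 0.5 | 0.5625 | 0.028 |
| 0.7 | 0.7375 | 0.037 |

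**Step 3: size of a chance imbalance.** SE of D = SD × √(2/105).
- At SD 0.25: 0.25 × 0.138 = 0.0345. Across SD 0.15 to 0.30 it is 0.021 to 0.041.
- A one-SE imbalance at ρ = 0.5 shifts the QALY difference by 0.0345 × 0.5625 = 0.019.

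**Step 4: variance explained.** With all visits equally correlated at ρ and SD set to 1, QALY variance = 0.40625 + 0.21875ρ + 0.375ρ.
- At ρ = 0.5 this is 0.703, and R² = 0.5625²/0.703 = 0.45.
- At ρ = 0.4 and 0.6, R² is 0.35 and 0.55.
- At R² = 0.45 the unadjusted comparison needs about 1/(1 − 0.45) = 1.8 times as many patients for the same precision.

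**Step 5: simulation of the remedy.** 4,000 runs, 105 per arm, SD 0.25, follow-up utilities correlated 0.6 with each other, and a treatment effect of 0.05 at both follow-ups. The true QALY difference is 0.05 × 0.875 = 0.044. The unadjusted difference is compared with regression on arm and baseline utility.

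| ρ | Slope on D, unadjusted | Slope on D, adjusted | SE, unadjusted | SE, adjusted |
|---|---|---|---|---|
| 0.3 | 0.38 | −0.005 | 0.029 | 0.026 |
| 0.5 | 0.58 | 0.012 | 0.030 | 0.022 |
| 0.7 | 0.74 | −0.001 | 0.030 | 0.017 |

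Both estimators average 0.043 to 0.044, in line with the true value. At ρ = 0.3 the simulated SEs (0.0260 against 0.0291 before rounding) imply that baseline explains 1 − (0.0260/0.0291)² ≈ 20% of the variance.

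**The case against.** **The section never says the analysis is unadjusted.** The ICUR wording is the general definition, which a covariate-adjusted mean difference also satisfies, and an article may leave the model to a fuller document. The first part stands: a reader might infer that the protocol commits to raw differences, and the text does not go that far. But the section does fix the number of bootstrap samples, discounting, analysis set, missing-data assumption and software, and names no covariate at any step. Followed as written, it yields an unadjusted result.

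**The clinical section shows an intention to adjust, also for secondary outcomes, and EQ-5D and CSRI are among them.** True, but that text sits under clinical efficacy and is not carried to QALYs, costs or the ICUR.

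**There is no bias.** A reader might infer that the QALY difference is biased. Under randomisation it is not, and the patient-level bootstrap already carries chance imbalance as sampling error. The acceptability curves would be less precise than they could be, not invalid. This stands, with one qualification: the complete-case set at 12 months is not protected by randomisation if dropout differs between arms.

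**The inputs are not fixed.** Visit timing differs between the abstract, the *Instruments* text and the Table 1 footnote. The direct weight stays at 0.125 so long as the first follow-up is at 3 months, but the later weights change. QALYs gained could also mean area net of the patient's own baseline. Imbalance would then enter with the opposite sign (0.5625 − 1 = −0.44 per unit at ρ = 0.5), and regression on baseline deals with that reading too.

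**Conclusion.** The point holds as a free improvement in precision and robustness on a secondary objective. A chance baseline utility difference passes partly into the QALY difference: 12.5% directly, and about 39% to 74% in total for correlations of 0.3 to 0.7. Under SD 0.25, correlation 0.5 and 105 per arm, a one-SE imbalance of 0.035 moves the QALY difference by about 0.02. Baseline utility explains about 45% of QALY variance, or about 20% to 55% for correlations of 0.3 to 0.6, depending on the correlation structure. The SD and correlations are assumptions.

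Two stronger readings are not supported. One is that a baseline difference passes in full into the result; the weights show that it does not. The other is that imbalance would reverse the sign of the ratio. The protocol article gives no expected QALY or cost difference against which to judge a shift of 0.02, so neither a reversal nor the movement in the ICUR can be sized from it.

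**What to change.** In *Cost-utility analysis*, state that incremental QALYs are estimated by regression of area-under-the-curve QALYs on arm, baseline EQ-5D utility and region. Region belongs in the model because allocation is blocked by region. Refit the model in each bootstrap sample, keeping each patient's cost and QALY together, and build the cost-utility plane and acceptability curves from the adjusted differences. Report the unadjusted difference as a sensitivity analysis.

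Adjusting incremental costs for the baseline three-month CSRI cost is a reasonable parallel step, but the protocol article gives no figures from which to quantify the gain.

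The cost is a few sentences of analysis text. Both baseline measures are already collected, and neither sample size nor visits change.

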### Sample size

The sample size of this study was based on the expected difference on the primary outcome variable, i.e. depressive symptoms, between the intervention groups and the Treatment as Usual group at post-test. Based on a power of 0.80 in a one-tailed test, an alpha of 0.05, we need 100 subjects in each condition to show an effect-size of 0.40.

Therefore, the total sample size was determined at 300. This sample size also allows calculating clinically significant difference in the main outcome variable, Beck Depression Inventory II. Based on previous studies [36], this difference has been placed at 5 points. It allows changing scoring from normality to mild depression or from mild to moderate depression. Taking account an expected withdrawal rate of 30% according to previous studies [9-14], a sample size of 450 patients (150 by arm) was calculated. The three participating health centers will select 150 patients with cluster randomization to allocate one third in each of the three arms.

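### The base-case cost-utility result rests on 12-month complete cases under an unsupported missing-completely-at-random assumption; the multiple imputation already planned should take its place

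*Protocol article*

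**What the plan says.** The Cost-utility analysis section of the protocol article makes three linked statements.

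- The assumption: "We assume that data will be missing completely at random". No justification follows.
- The analysis set: "Only patients with both cost and relevant outcome data at 12-month follow-up will be included in the cost-utility analyses".
- The place of imputation: missing 12-month values will also be imputed, but as a sensitivity analysis to test robustness. "The imputations will be performed using the multiple imputation procedure in STATA 11.0".

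Other sections bear on this:

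- Sample size plans for loss: "Taking account an expected withdrawal rate of 30% according to previous studies", with 450 patients in total and 150 per arm.
- Interventions describes unequal contact. In the low-intensity arm a trained researcher contacts patients and urges them to finish on time. The self-guided arm has technical support only. The ITAU arm has no programme during the study.
- Table 1 schedules BDI-II, EQ-5D and the service-use inventory at baseline and at every follow-up session, so patients missing at 12 months will usually have earlier data.

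**The concern.** Missing completely at random means that patients without 12-month data are a random subset of those randomised: same arm mix, severity, utility and cost. In a trial where one arm is prompted by a therapist, one is left alone with a program and one has no program, that needs an argument, and none is given. Missingness could plausibly depend on arm and on how depressed the patient is. Both are recorded.

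Two things are at stake. The incremental cost-utility ratios and acceptability curves from the base case would describe the patients with complete 12-month data, not everyone randomised. And the earlier data of the excluded patients, which could correct for missingness related to measured severity, would play no part in the main result. Cost-effectiveness is a stated secondary objective, so this is a result that readers will use.

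**Working it through.** **Inputs from the article.** 450 patients, 150 per arm; 300 before allowance for loss; 30% expected withdrawal (Sample size). Assessments at baseline, 3 and 12 months (Abstract). QALYs by area under the curve (Cost-utility analysis).

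**Inputs that are assumptions.** Dropout by arm, and the difference between completers and dropouts. The article gives neither, so a range is shown.

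**Step 1. The plan's own figure.** 300 / (1 − 0.30) = 429, not 450; 450 corresponds to a loss of 1 − 300/450 = 33.3%. The planned number is therefore a little more generous than 30% requires. The point does not depend on this; it uses only the 450 and the 30%.

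**Step 2. Who leaves the base case.** 450 × 0.30 = 135 excluded and 315 kept. Spread evenly, that is 45 excluded and 105 kept per arm.

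**Step 3. Bias in a between-arm difference.** In one arm let d be the proportion missing and g the completer mean minus the dropout mean. The mean over everyone is the completer mean minus d × g, so completers overstate the arm by d × g. The complete-case difference is therefore off by

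bias = d_T × g_T − d_C × g_C,

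with T the programme arm and C the comparator. Missing completely at random sets g to zero in every arm, so it assumes the bias away.

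| Dropout T / C | Gap T / C (QALY) | Calculation | Bias (QALY) |
|---|---|---|---|
| 30% / 30% | 0.10 / 0.10 | 0.030 − 0.030 | 0 |
| 30% / 30% | 0.10 / 0.05 | 0.030 − 0.015 | +0.015 |
| 30% / 30% | 0.05 / 0.10 | 0.015 − 0.030 | −0.015 |
| 35% / 20% | 0.05 / 0.05 | 0.0175 − 0.010 | +0.0075 |
| 35% / 20% | 0.10 / 0.10 | 0.035 − 0.020 | +0.015 |

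The 35% / 20% rows agree with the planned overall rate if both programme arms lose 35%: (35 + 35 + 20) / 3 = 30%.

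**Step 4. The same for costs.** If dropouts cost 300 to 500 euros more than completers in both arms (assumed), 35% against 20% dropout shifts the cost difference by 0.35 × (−300) − 0.20 × (−300) = −45 euros, up to 0.35 × (−500) − 0.20 × (−500) = −75 euros.

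**Step 5. Scale.** The gaps above are in QALYs over the whole year. If the 0.10 gap applied to the 12-month utility alone, the last row would give 0.015 in utility at that visit. With visits at 0, 3 and 12 months the 12-month value has weight (9/12)/2 = 0.375, so the QALY shift from that visit is 0.015 × 0.375 ≈ 0.006.

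**The case against.** The best defence is that the plan already contains the remedy. Multiple imputation of the 12-month data is promised, so a material discrepancy would be visible. That softens the point without removing it: the headline ratio and curves remain those of complete cases, on a premise that nothing supports.

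A second defence is that stopping the modules is not the same as missing an assessment. Follow-up measures are collected by a researcher, and service use is recorded in all three arms. This is right. The 30% is an expected withdrawal rate, and the share lacking 12-month data may be higher or lower. A reader might treat 30% as a floor because the forecast dates end recruitment in December 2013 and monitoring in June 2014. Loss from a calendar cut-off, however, is administrative and closer to random, so it does not support the selection argument.

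Three stronger readings are tempting, and the article does not support them.

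- *The complete-case set contradicts intention to treat.* The statement "The analysis will be per intent to treat and will follow CONSORT recommendations" stands under the heading on clinical efficacy, and the economic set is defined separately. Two analyses have two sets, which is a difference of approach and not a contradiction.
- *The bias flatters the programme.* The article gives no dropout by arm and no completer-dropout difference. Step 3 shows zero, positive and negative results under equally simple assumptions. That completers are self-selected is likewise an inference.
- *The incremental ratio is wrong because it is unadjusted for baseline utility and cost.* The ratio is "defined as the difference in mean costs divided by difference in mean QALYs", a general definition that adjusted means also satisfy. How the means are estimated is detail that an article may leave out. Chance imbalance at baseline is sampling variation, not bias.

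**Conclusion.** The concern holds as a weakness of a stated analysis choice. The base-case cost-utility result is limited to patients with 12-month cost and outcome data, on an assumption for which the article gives no reason and which its own design makes doubtful. If the expected 30% withdrawal translates into missing 12-month data, about 135 of 450 patients and their earlier measurements drop out of the main result.

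Whether this produces bias cannot be read from the article. The bias is zero when dropout and the completer-dropout gap are equal across arms. Under the assumed values above it is about 0.015 QALY in either direction, and smaller if the gap is confined to the last visit. The change is worth making because it uses data already collected, relies on a weaker assumption and costs little. It should be made, but it does not touch the primary BDI-II analysis.

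**What to change.** Swap the ranks of the two analyses, and drop the sentence assuming that data are missing completely at random.

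- **Base case:** all randomised patients, with multiple imputation under missing at random. Impute separately by arm from baseline and interim EQ-5D, costs and BDI-II, and from region. Combine the imputation with the planned 1,000 bootstrap samples, and state how the two are nested, so that the ratios and acceptability curves carry both sources of uncertainty.
- **Sensitivity analyses:** the complete-case analysis as now written, and a missing-not-at-random analysis that shifts the imputed utilities and costs, including by different amounts in different arms. Imputation under missing at random corrects only for what was measured, so the shift is needed to show how far the conclusion depends on that.
- **Optional, for precision and not as a correction:** estimate incremental QALYs and costs with adjustment for baseline EQ-5D index, baseline three-month cost and region.

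The cost is revised wording and a little more analysis work. The imputation is already planned, and no extra visit, instrument or patient is needed.
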